## Screening examination and eligibility screening form

All legal guardians/subjects must sign and date the most current IRB/IEC-approved written informed consent/assent (where appropriate) before any study-specific assessments or procedures are performed.

The assessments in Table 2 must be obtained within a period of no more than 8 weeks before the subject is randomized, except as noted. Subjects must fulfill all the entry criteria for participation in the study (see Sections 6.2 to 6.3). An Eligibility Screening Form (ESF) documenting the investigator’s assessment of each screened subject with regard to the protocol’s inclusion and exclusion criteria is to be completed by the investigator. A screen failure log must be maintained by the investigator.

Table 2 Screening Assessments

| Medical history and physical examination | Includes family history of HBV, concomitant medication (including for CHB), and vital signs (blood pressure, heart rate, temperature). |
| --- | --- |
| Ophthalmological examination | By ophthalmologist and including fundoscopic examination, visual acuity assessment, visual field testing, and color visual testing. Any subject who develops ocular symptoms should receive a prompt eye examination by an ophthalmologist and additional examinations as necessary. |
| Ultrasound and liver elastography | To rule out hepatocellular carcinoma and liver cirhosis. Further liver imaging assessment may be performed if necessary. |
| Liver biopsy | Optional |
| HCG pregnancy test | For females of childbearing potential, a negative urine or serum HCG test needs to be documented within 24 hours prior to baseline. Note that the test may be performed at the baseline visit, provided that the result is available prior to randomization and commencement of treatment. |
| Hematology | Complete blood count (hemoglobin, hematocrit, total white blood cell [WBC] count, differential WBC count [neutrophils, lymphocytes, monocytes, eosinophils, basophils]), platelet count, international normalized ratio (INR) |
| Clinical chemistry | ALT, AST, GGT, total bilirubin, alkaline phosphatase, total |
|  | protein, albumin, blood urea nitrogen (BUN)/urea, creatininee, uric acid, total calcium, phosphorus, cholesterol, triglycerides, random glucose, sodium, chloride, potassium |
| Urinalysis | Dipstick with subsequent microscopic evaluation if positive for blood |
| Immunology and special chemistry | Alfa-fetoprotein, ANA, anti-HAV IgM, anti-HCV, anti-HIV, anti-  HDV, anti-HEV IgM |
| HBV serology and virology | HBeAg, anti-HBe, HBsAg, anti-HBs, quantitative HBsAg and  HBeAg, HBV-DNA |
| Thyroid function tests | FT3, FT4, TSH |

## Procedures for enrollment of eligible subjects

A subject will be enrolled in the study and assigned a screening number after the subject has given informed consent/assent. Once a subject has fulfilled the entry criteria they may be randomized or assigned, as applicable.

The subject randomization numbers will be generated by SAS PROC PLAN with a block size of 6 and were communicated to the sites in sealed envelopes prepared by the statistician based on the randomization sequence. The investigator or designee will use the CRF with the assigned subject number and enter the corresponding number for allocation to the study groups in the appropriate place on each subject’s CRF.

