# 4. Study design

## Overview of study design

This study is a multi-center, randomized, prospective, open-label Phase IV clinical trial (Fig 1), CHB patients who had HBV DNA<1000 copies/ml and HBsAg<3000 IU/ml by NAs treatment, were randomized at a ratio of 1:1:1 to one of 3 groups as follows:

Arm A: ETV 0.5mg once daily for 96 weeks

Arm B: Peg-IFN-α-2b 180 ug/week S.C. for 96 weeks plus ETV 0.5mg once daily from day 1 to 48 weeks

Arm C: Peg-IFN-α-2b 180 ug/week S.C. for 96 weeks plus ETV 0.5mg once daily from day 1 to 48 weeks plus GM-CSF from day 1 to 48 weeks

[figure not shown]

Fig 1. Study design

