## Assignment to treatment groups

All the eligible patients were randomly assigned in a 1:1:1 to one of three groups. We used interactive web response system (IWRS) for computer-generated randomisation sequences with a predefined stratification scheme. Randomisation was stratified by HBeAg (positive or negative) state and gender (male or female) at enrolment. A patient will be enrolled in the study and assigned a patient number after all protocol eligibility requirements have been met. The investigator will use the appropriate patient’s Case Report Form (CRF) and record the patient’s allocated treatment or treatment number in the CRF. It is the investigator’s responsibility to ensure that each patient receives the assigned treatment.

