## Centers

This study will be conducted in 6 centers in China. These centers ere qualified by training and experience in the management of patients with HBV. Each center in expected to contribute at least 40-50 patients over the course of approximately 12 months.

Recruitment will be competitive.

List of study centers:

1. Department and Institute of Infectious Disease, Tongji Hospital, Tongji Medical College, Huazhong

University of Science and Technology, Wuhan, China

1. Department of Infectious Disease, The First Affiliated Hospital of Wenzhou Medical University,

Wenzhou, China

1. Beijing You'an Hospital, Capital Medical University, Beijing, China
2. Liver Research Center, First Affiliated Hospital of Fujian Medical University, Fuzhou, China
3. Department of Infectious Diseases, Xiangya Hospital, Central South University, Changsha, China
4. Department of Infectious Disease, Shengjing Hospital of China Medical University, Shenyang, China

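### The protocol gives two conflicting allocation mechanisms, a stratified IWRS and sealed site envelopes with a published fixed block of 6; in this open-label trial the envelope version would weaken concealment.

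*Protocol*

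**What the plan says.** Protocol section 4.3 (Assignment to treatment groups) sets a 1:1:1 ratio and names the system: "We used interactive web response system (IWRS) for computer-generated randomisation sequences with a predefined stratification scheme". It then gives the factors: "Randomisation was stratified by HBeAg (positive or negative) state and gender (male or female) at enrolment". That makes 2 x 2 = 4 strata. Centre is not a factor.

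Protocol section 7.3 (Procedures for enrollment of eligible subjects) describes the same step differently. There the numbers are "generated by SAS PROC PLAN with a block size of 6 and were communicated to the sites in sealed envelopes prepared by the statistician". This section does not mention the web system or the strata, and it does not say whether blocks run within site, within stratum or across the whole trial.

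Two other statements matter. On blinding, section 4.1 (Overview of study design) says: "This study is a multi-center, randomized, prospective, open-label Phase IV clinical trial". On sites, section 4.5 (Centers) says: "This study will be conducted in 6 centers in China". No section makes the envelopes a backup for the web system, or the reverse.

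**The concern.** A site that follows 4.3 requests each allocation from a central system. A site that follows 7.3 opens the next envelope in its own stock. These are different procedures with different protection against foreknowledge.

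Under 7.3, three facts combine. The envelopes are at the site, every earlier allocation is visible because treatment is open, and the block size is one fixed value in a document that investigators hold. Staff who keep count can sometimes know the next arm, and more often rule one out.

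The protocol also leaves room to act on that knowledge. Screening may run for up to 8 weeks before randomisation. Quantitative HBsAg is measured at screening, and the synopsis caps it at 3000 IU/ml. The background section says that HBsAg loss follows a fall in HBsAg, so a patient's starting level is plausibly prognostic.

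Few events are expected, so a small number of steered patients could matter. With 80-100 patients per arm, the assumed 0-3% on ETV is 0 to 3 losses (100 x 0.03). The assumed IFN rates, 3-10% in the Sample Size section and 10-20% in section 4.2, span about 2 losses (80 x 0.03 = 2.4) to 20 (100 x 0.20). The tests named for categorical outcomes, chi-square or Fisher, do not adjust for baseline HBsAg.

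**Working it through.** The protocol states no predictability figure, so there is none to reproduce.

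**Inputs from the protocol.** Three arms at 1:1:1 (4.3); block size 6, hence 2 + 2 + 2 (7.3); open-label (4.1); 6 centres with at least 40-50 patients each (4.5); 4 strata (4.3); total N 257 (synopsis).

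**Assumption.** The level at which blocks run is not stated, so the result is given for three cases.

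**Step 1: one complete block seen at one site.** There are 6!/(2!2!2!) = 90 possible orders. An allocation is certain when only one arm is left in the block.

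- Position 6 is always certain.
- Position 5 is certain when the last two slots are the same arm: 3 x C(2,2)/C(6,2) = 3/15 = 1/5.
- Positions 1 to 4 are never certain.

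Expected share certain: (1 + 1/5)/6 = 1.2/6 = 20%.

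Exactly one arm can be ruled out with probability 1/5, 3/5 and 4/5 at positions 3, 4 and 5. That is 1.6/6 = 26.7%. At least one arm can be ruled out in 20% + 26.7% = 46.7%. For a given arm such as ETV, the expected number of positions after its second slot is (6 - 2)/3 = 1.33, and 1.33/6 = 22.2%.

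The best guess is right with probability 1/3, 2/5, 1/2, 8/15, 3/5 and 1 at positions 1 to 6. The average is 56.1%, against 33.3% by chance.

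**Step 2: incomplete last blocks and the level of blocking.**

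| How blocks run | Calculation | Certain in advance |
|---|---|---|
| One list per site, 40 patients | 6 full blocks: 6 x 1.2/40 | 18.0% |
| One list per site, 50 patients | 8 full blocks: 8 x 1.2/50 | 19.2% |
| One list per site, 257/6 = 42.8 | 8.4/42 and 8.4/43 | 20.0% and 19.5% |
| One list per site, random centre sizes | simulation | about 19% |
| Site x 4 strata, 257/24 = 10.7 | 1.2/10 and (1.2 + 0.2)/11 | 12.0% and 12.7% |
| Site x 4 strata, random cell sizes | simulation | about 16% |
| Central, 4 strata, site sees only its own patients | simulation, 6 equally likely centres, block 6, N = 257 | about 0.01% |

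Out of 257 patients this is about 46 to 51 certain allocations (18-20%), about 31 to 41 (12-16%), or essentially none.

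**Step 3: other fixed block sizes, if seen at one site.** With k = B/3, the share is the sum over j = 1 to k of 3 x C(k,j)/C(B,j), divided by B. This gives 33.3% for a block of 3, 20.0% for 6, 14.3% for 9 and 11.1% for 12.

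**The case against.** The strongest reply is that the two sections overlap more than they clash. Sequences made in SAS PROC PLAN are computer-generated, and a block of 6 fits a stratified permuted-block scheme. Section 7.3 does not repeat the strata, but envelopes can be prepared by stratum. Nothing gives 7.3 precedence, and if 4.3 is what operated, foreknowledge is negligible. All of this stands. The conflict is over how the allocation reaches the site, web system or envelope, and there it is complete.

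A reader might infer more than the documents support, in four ways:

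- **That one allocation in five is certain in this trial.** The 20% is the complete-block value for unstratified envelopes with blocks within site. The level of blocking is not stated, and the range runs from near 0% to 20%.
- **That 7.3 abolishes stratification.** Silence is not denial, and 4.3 states the factors expressly.
- **That 7.3 overrides 4.3.** No text says so.
- **That patients were steered.** Nothing in the protocol shows this. The point concerns opportunity only.

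It may also be said that the time for change has passed. Section 4.3 is in the past tense and the synopsis gives an exact total of 257, so randomisation may be finished. That alters the remedy but leaves the contradiction in place.

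**Conclusion.** Wrong as written: an internal contradiction on how patients are allocated. It goes beyond missing detail, because one of the two descriptions would weaken concealment in an open-label trial and the resulting selection bias could not be removed in the analysis.

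The size depends on which description was followed: double-digit predictability under site envelopes, near zero under the central system. The envelope figures rest on three conditions. Blocks run within site, which is the natural reading of envelopes sent to sites but is not stated. Staff know the block size, which is printed in the protocol. Staff keep track of earlier allocations, which open treatment allows. The near-zero figure assumes that each site sees only its own patients.

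**What to change.** **If randomisation is not complete.** Make the central web system, stratified by HBeAg status and gender as in 4.3, the only mechanism. Delete the envelope text from 7.3. Move the block size and the level of blocking to a document that sites do not hold. Varying block sizes are an optional extra, since the central system already brings predictability close to zero; if they are used, avoid blocks of 3, which are the most predictable when seen at a site (33.3%). The cost is an amendment to wording, as the web system is already planned.

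**If randomisation has taken place.** State which mechanism was used and whether the strata applied to it. If envelopes were used, disclose this with the level at which blocks ran, and report baseline HBsAg by arm and by position within block. That table can reveal steering but cannot correct for it. The cost is a short statement and one table built from the retained randomisation list.

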## Clinical assessments and procedures

A baseline visit will be performed, and for subjects in three groups all baseline assessments and procedures must occur prior to administration of the first dose of study drug. Subjects will subsequently be seen for evaluation at the following timepoints:

During treatment period: Day 1, Week 2, 4, 8, 12, 16, 20, 24, 28, 32, 36, 40, 44, 48, 52, 56, 60, 64, 68, 72, 76, 80, 84, 88, 92 and 96

During follow-up: Week 24 post-treatment

Any subject who discontinues study treatment should return to complete assessments as per the Week 96 visit.

### Efficacy

Efficacy (see Section 5.1 for primary and secondary endpoints) will be determined from assessment of loss of HBsAg, HBsAg positivity and seroconversion, HBeAg loss, HBV-DNA and ALT.

### Safety

Safety assessments will include symptom directed physical examination, vital signs, review of concomitant medications, reported AEs and specified safety laboratory assessments of hematology, clinical chemistry, thyroid function, and urinalysis.

Additional safety assessments will be determined from premature withdrawals from treatment for safety or tolerability reasons.

All subjects need to have ophthalmological examination (including fundoscopic examination, visual acuity assessment, visual field testing, and color visual testing) by an ophthalmologist. Thereafter, subjects treated with IFN will receive ophthalmological examination as per the schedules in Table 1. Any subject who develops ocular symptoms should receive a prompt eye examination by an ophthalmologist and additional examinations as necessary.

For females of childbearing potential, a pregnancy test will be performed within 24 hours prior to baseline. This could be performed at the baseline visit, provided that the result is available prior to randomization and commencement of treatment. In addition, subjects will have pregnancy tests performed as per the schedules in Table 1.

## Laboratory assessments

Laboratory assessments post-screening are noted in Table 3 and will be carried out as per the schedules in Table 1.

Table 3 Laboratory Assessments

| Hematology | Complete blood count (hemoglobin, hematocrit, total white blood cell [WBC] count, differential WBC count [neutrophils, lymphocytes, monocytes, eosinophils, basophils]), platelet count, international normalized ratio (INR) |
| --- | --- |
| Clinical chemistry | ALT, AST, GGT, total bilirubin, alkaline phosphatase, total protein, albumin, blood urea nitrogen (BUN)/urea, creatininee, uric acid, total calcium, phosphorus, cholesterol, triglycerides, random glucose, sodium, chloride, potassium |
| Urinalysis | Dipstick with subsequent microscopic evaluation if positive for blood |
| Immunology and special chemistry | Alfa-fetoprotein, ANA |
| HBV serology and virology | HBeAg, anti-HBe, HBsAg, anti-HBs, quantitative HBsAg and  HBeAg, HBV-DNA |
| Thyroid function tests | FT3, FT4, TSH |
| HCG pregnancy test | For females of childbearing potential, subjects will have pregnancy tests performed as per the schedules in Table 1. |

HBsAg will be assessed by the central laboratory. Other parameters will be assessed by a local laboratory, normal ranges for the local laboratory parameters must be supplied to designee before the study starts and at any point that the normal ranges are changed.

## Subject medication diary review

Subjects will complete a Subject Medication Diary (SMD), which the patients will bring to each study visit. The information will be reviewed by the Clinic Coordinator at each study visit. It is mandatory that each drug dose be recorded in the SMD. The patient/guardian will be instructed to record the date and dose of study drug. The person giving the medication must initial the SMD.

During the diary review, the reviewer will correct unreadable information and ask the subject to supply missing information. Reviewers will report missing doses, dose adjustments, and treatments stops or restarts on the CRF. Subject diaries will be maintained with the source documents at each site.

## Concomitant medication and treatment

Use of any investigational drugs as a result of participation in another clinical study is prohibited during the study including the extended long-term follow-up period.

Concomitant use of any other investigational drugs (e.g., compassionate use), immunomodulatory treatments (e.g., systemic corticosteroids), growth factors (e.g., erythropoietin) or antiviral treatments with anti-HBV activity (e.g., lamivudine, tenofovir, emtricitabine, adefovir, telbivudine, systemic acyclovir, systemic famciclovir) other than those specifically allowed by this protocol are prohibited during either the treatment period or follow-up, in order to minimize the confounding effects of such treatments in determining treatment responses.

Exceptions to this are as follows:

Subjects with significant deterioration in hepatic function who permanently discontinue study drug and need to consider NA therapies in group II and group III, treatments with anti-HBV activity will not be prohibited during follow-up period.

Herbal, botanical, and other agents that are traditionally used for chronic HBV disease are discouraged.

All concomitant medications should be reported to the investigator and recorded on the appropriate electronic Case Report Form (CRF), including details of any previous anti-HBV treatment, as well as any other previous concomitant medications taken within 6 months

prior to baseline.

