Focusing on increasing the rate of HBsAg loss, the central goal of national "Twelfth Five-Year" viral hepatitis plan, our study proposes a multi-target combination intervention to improve HBsAg loss rate for CHB patients who had received long-term NAs treatment but not achieved HBeAg seroconversion. Based on the data from previous OSST study, the sequential combination therapy of NAs and IFN are designed, and the immunomodulatory factor GM-CSF is added timely. It is planned to establish a cohort in multiple centers and fulfill the new treatment strategy.

This study intends to adopt a prospective, multi-center, randomized, controlled, open-labeled trial design. The enrolled CHB patients will be assigned to three treatment groups according to the principle of random (1:1:1). Patients in Group I are treated with ETV for 96 weeks; patients in Group II are treated with Peg-IFN for 96 weeks, combined with ETV during the first 48-week; Group III are treated with Peg-IFN for 96 weeks, combined with ETV and GM-CSF during the first 48-week. All patients will be followed-up for 24 weeks after treatment. It is expected that the HBsAg loss rate in Group II and III will increase by more than 10% compared with Group I after treatment, which indicates a better clinical outcome. The success of this project will improve the treatment efficacy of existing antiviral therapy, and enable CHB patients to safely stopping NAs in advance to avoid drug resistance. More importantly, amounts of CHB patients with suboptimal treatment efficacy will obtain HBeAg seroconversion even HBsAg seroconversion, which can reduce the occurrence of liver cirrhosis and liver cancer. It will produce huge social and economic benefits.

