## Statistical methods

### Primary Variables

The primary efficacy parameter is HBsAg loss at end of treatment and 24 weeks after the end of treatment. Subjects with missing values for this parameter will be considered non-responders.

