### Secondary Variables

All secondary variables will be determined at end of treatment and 24 weeks after the end of treatment.

1. HBsAg positivity (defined as presence of anti-HBs) and seroconversion (defined as loss of HBsAg and presence of anti-HBs)
2. Proportion of patients who achieve undetectable HBV DNA
3. Quantitative HBsAg measurement
4. HBeAg seroconversion (defined as absence of HBeAg and presence of HBeAb in

HBeAg negative patients)

1. ALT normalization (defined as ALT measure ≤ ULN)
2. Sustained virologic response at the end of follow-up

Histology improvement (option)

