### Analysis populations: ITT and mITT population

The ITT population shall include all subjects who receive at least one dose of study medication. For the ITT population, subjects will be analyzed according to the groups to which they were randomized.

A modified ITT (mITT) analysis was conducted, excluding patients who failed to meet inclusion criteria at baseline prior to randomization. Any patients including in mITT analysis who withdrew from the study, for whatever reason, was classified as a non-responder.

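### No analysis rule covers Peg-IFN-arm patients who start an NA during follow-up, so their on-drug ALT and HBV DNA values are scored as they stand

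*Protocol*

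**What the plan says.** **Rule and exception.** Under Concomitant medication and treatment, anti-HBV drugs outside the protocol regimen "are prohibited during either the treatment period or follow-up, in order to minimize the confounding effects of such treatments in determining treatment responses". The one exception is for patients with significant hepatic deterioration "who permanently discontinue study drug and need to consider NA therapies in group II and group III"; for them "treatments with anti-HBV activity will not be prohibited during follow-up period". Group I is not mentioned.

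**Follow-up is off study drug in every arm.** Group I receives "ETV 0.5mg once daily for 96 weeks" (Overview of study design), and Background and Rationale states: "All patients will be followed-up for 24 weeks after treatment". Assessment of Compliance rules out treatment beyond the allocated duration for any subject.

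**Scoring.** The chapter headed *The complete statistical analysis plan* has two non-responder rules:
- Primary Variables, on HBsAg loss: "Subjects with missing values for this parameter will be considered non-responders".
- Analysis populations, for any mITT patient "who withdrew from the study, for whatever reason, was classified as a non-responder".

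**Endpoints exposed.** Secondary Variables sets undetectable HBV DNA and ALT at or below ULN at end of treatment and 24 weeks later, with no condition on NA use. It also lists "Sustained virologic response at the end of follow-up" without defining it.

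**The concern.** The protocol itself names non-study anti-HBV drugs as a confounder of response. It then permits them in the two experimental arms only, and gives the analysis no instruction for the patients concerned. A patient whose liver function deteriorated after Peg-IFN, who started an NA and who has a result 24 weeks after treatment can be counted as having normal ALT or undetectable HBV DNA because of the NA. A treatment failure then enters the comparison as a success, and the permission that allows this exists only on the Peg-IFN side. What is at stake is the post-treatment comparison of ALT and HBV DNA, where the reader wants to know what persists without drug.

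**Working it through.** **1. Does any stated rule reach the patient?** Take a Group II or III patient who deteriorates, permanently stops study drug, starts an NA in follow-up and is assessed 24 weeks after treatment.

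| Rule | Scope | Applies? |
| --- | --- | --- |
| Missing value (Primary Variables) | HBsAg loss only | No: the value is observed, and the endpoints here are others |
| Withdrew from the study (Analysis populations) | mITT | No: the exception places the patient in follow-up, still in the study |
| Off-drug condition (Secondary Variables) | HBV DNA, ALT | None stated |

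Clinical assessments and procedures also has treatment discontinuers return for assessment, so stopping drug is not leaving the study. By default the observed, on-drug value is used.

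**2. Which endpoints have a value at that visit?** Table 1 schedules biochemistry, including ALT, at week 120. As extracted, it marks HBV DNA at week 108 and not at week 120, whereas the endpoint sections require it 24 weeks after treatment. The ALT part therefore rests on both schedule and endpoint text; the HBV DNA part rests on the endpoint text alone.

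**3. Inputs for the size.** The protocol gives no figure for this effect to reproduce.
- Arm size: 257 in total (Synopsis), 257 / 3 = 85.7, so n = 86 per arm.
- On-NA response *r*: 0.67 to 0.90, the HBV DNA rates after 48 weeks of ETV in HBeAg-positive and HBeAg-negative patients in the protocol's ETV section. The ALT rates there, 68% and 78%, lie within that range. Follow-up here lasts 24 weeks, so these figures are only a guide.
- Share of a Peg-IFN arm starting an NA, *f*: not stated; assumed 2%, 5% or 10%.
- Response among everyone else: assumed 50%.
- The same share *f* of Group I deteriorates and none of them responds: assumed.
- Two-sided 5% chi-square test without continuity correction: level assumed.

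**4. Formulas.** Group I rate = (1 − *f*) × 0.5. Peg-IFN rate = (1 − *f*) × 0.5 + *f* × *r*. Inflation = *f* × *r*. The false-difference probability is the exact binomial probability that the test rejects at these two rates, although the arms do not differ off drug.

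**5. Results, n = 86 per arm.**

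| *f* | Patients (86 × *f*) | Group I rate | Peg-IFN rate, *r* = 0.67 / 0.90 | Inflation, points | False difference |
| --- | --- | --- | --- | --- | --- |
| 0 | 0 | 50.0% | 50.0% / 50.0% | 0 | 5.6% |
| 2% | 1.7 | 49.0% | 50.3% / 50.8% | 1.3 / 1.8 | 6.0% / 6.3% |
| 5% | 4.3 | 47.5% | 50.9% / 52.0% | 3.4 / 4.5 | 8.0% / 10.0% |
| 10% | 8.6 | 45.0% | 51.7% / 54.0% | 6.7 / 9.0 | 15.4% / 23.4% |

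The 5.6% with no rescue is the actual level of the nominal 5% test at these inputs. Under these assumptions the shift always favours Peg-IFN.

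**The case against.** **The effect may be tiny.** The exception needs significant hepatic deterioration, permanent discontinuation and a need to consider NA therapy, in a population without cirrhosis or decompensation. At 10%, nearly 9 of 86 patients in an arm would have to meet it. This stands: at 2% the effect is negligible, and only secondary endpoints of a self-described pilot are involved.

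**Such patients may be withdrawn anyway.** Criteria for premature withdrawal uses the word for both treatment and study, and lets the investigator withdraw subjects for adverse events, which would make them mITT non-responders. That can happen, but it is discretionary, and the exception expressly foresees patients who remain in follow-up.

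**Observed values by randomized arm are a legitimate choice, and the handling could sit in a separate plan.** Both are fair in general. Here the chapter presents itself as complete and already fixes non-responder rules, while the protocol calls these drugs a confounder of response. If as-observed scoring is intended, it should be stated.

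**Stronger readings that the text does not support.** A reader might infer that deterioration in Group I is scored as failure. No section says so: Group I is scored on observed values too. The asymmetry lies in what is permitted, and zero response in comparable Group I patients is an assumption of the calculation. A reader might also infer that rescued patients count as sustained virologic responders. That endpoint is undefined, so it cannot be said either way. Nor is every affected assessment at week 120: for early discontinuers, 24 weeks after the end of treatment falls sooner.

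**Conclusion.** The gap is real, and it is limited to secondary endpoints. As written, a Group II or III patient who starts an NA under the exception and stays in follow-up contributes an on-drug value to ALT normalization and, on the endpoint text, to undetectable HBV DNA 24 weeks after treatment. The bias can run towards Peg-IFN because only those arms have the permission. Its size cannot be read from the protocol: the table above rests on an assumed rescue share, 50% response otherwise, borrowed on-ETV rates and no response in comparable Group I patients. The narrow exception makes the 2% row (under 2 points, false-difference probability about 6%) more plausible than the 10% row. HBsAg loss, the primary endpoint, is little affected. The correction is worth making because it is cheap and the protocol's own reasoning calls for it.

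**What to change.** In Secondary Variables, add that any patient, in any arm, who starts anti-HBV therapy outside the assigned regimen before the assessment 24 weeks after end of treatment is a non-responder at that assessment for undetectable HBV DNA, ALT normalization and sustained virologic response. Tie the rule to that assessment and not to week 120, so that it also fits early discontinuers. Define sustained virologic response as an off-treatment outcome. Report the number of such patients per arm, with an as-observed analysis as sensitivity. Reconcile the HBV DNA follow-up visit in Table 1 (week 108 as extracted) with the endpoint sections.

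Cost: a few lines of analysis wording and slightly lower Peg-IFN response rates at follow-up. The data needed are already collected, since concomitant medications must be recorded on the CRF. No clinical rule changes.
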